### Data analysis

Analysis will follow intention-to-treat principles: outcome data will be sought and included in the analysis for all patients irrespective of receipt of the intervention during the time scale of the trial. The CONSORT statement for cluster RCT's will be followed. Treatment effects for the cluster (ward) level outcomes will be estimated using appropriate mixed models with a fixed effect for ward gender, and a random intercept for the ward.

Individual (patient/staff) level outcomes measures will be analysed using an appropriate generalised linear mixed model with random intercepts for wards. With the exception of patient ward atmosphere (VOICE), the baseline values of the outcomes can be used as a covariate in the models.

A statistical analysis plan for primary and secondary outcomes, including sub-group analyses will be presented to and agreed with the programme steering group prior to the allocation codes being revealed and commencement of any data analysis. There are no planned interim analyses.

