### Outcome measures

Co-primary outcome measures have been selected. The first measure is total number of serious incidents (risky behaviours) per ward. We will be collecting serious incidents at baseline, 3-month follow-up, 6-month follow-up and 9-month follow-up. The data will be requested for the prior 3 months and will include incidents that fall into the categories of self-harm and violence (to staff, patients, and others).

All Trusts involved in the study are already required to collect ward level data on serious incidents as part of standard practice. Reporting criteria and procedures for serious incidents will be reinforced by senior managers in both intervention and control wards recruited to the study to sensitise all participating wards to reporting risk. As an additional protection against bias, blind assessors will collate data of staff-reported serious incidents and complete a 25% check across the 34 wards to ensure that they meet well operationalised definitions utilised in our previous research [15, 22].

The second primary outcome measure will be patient well-being as assessed by the Warwick-Edinburgh Mental Well-being Scale (WEMWBS; http://www2.warwick.ac.uk/fac/med/research/platform/wemwbs), which is a patient-reported health measure that will be collated at the individual patient level by blind assessors. The WEMWBS is used widely by IAPT for SMI and previous studies show that it is rated favourably by patients [23].

Despite the argument for the importance of serious incidents, we recognise the equally important value of targeting and assessing patient-reported outcome measures and will therefore measure patient mental well-being.

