### Sample size

The recruitment target is thirty-four wards. Based on a recent survey of acute inpatient wards across the NHS, it is estimated that there will be an average of 24 beds per ward (range 18-30) giving a pool of 816 patients at baseline across 34 wards. Based on the same survey, it is estimated that there will be an average of 25 staff per ward giving a potential pool of 850 staff across 34 wards. Based on trials of psychological therapy in inpatient settings [27, 30] it has been conservatively estimated that recruitment rates for the completion of individual level outcome measures at baseline will be 80% of eligible staff and 50% of eligible patients giving a pool of 680 staff and 408 patients.

For the primary outcome of number of serious incidents on the ward, assuming 5.22 mean number of events in the control arm [31], 16 wards per arm has more than 80% power to detect a reduction in mean number of events to 3.13 (40% relative reduction), assuming a poisson distribution for the outcome. To allow for possible dropout of a ward, we will recruit 34 wards in total.

For the individual level health related primary outcome (WEBWBS) and other individual level secondary outcomes, we used the –clustersampsi- command in Stata. We assume a between group effect size of 0.4 and an intra-cluster correlation coefficient of 0.05. We allow for a baseline-endpoint correlation of 0.3, which we suggest is conservatively low given the short time span between baseline and endpoint. We specified 85% power, 5% significance level, and calculated the average cluster size (i.e. how many participants were required to be recruited in each cluster). The optimal design for these parameters requires 9 participants per cluster. This leads to a total sample size per arm of 153, and 306 for the analysis set. Accounting for attrition of 20%, by making an adjustment to this value, 383 participants are required at baseline. This assumes that attrition is consistent across treatment arms and clusters. Therefore the aim is to recruit 34 clusters with 11 participants in each cluster, giving a total sample size at baseline of 384. Adjustments will be made for additional covariates in order to preserve 85% power against a larger observed ICC value or a weaker observed baseline-endpoint correlation.

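### The ward-level incident model should name the baseline 3-month incident count as a covariate: the protocol mentions baseline adjustment only for individual-level outcomes, and only as optional

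*Protocol article*

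**What the plan says.** The Outcome measures section of the protocol article defines the co-primary: "The first measure is total number of serious incidents (risky behaviours) per ward". It then gives the collection times: "We will be collecting serious incidents at baseline, 3-month follow-up, 6-month follow-up and 9-month follow-up". Each request covers the preceding three months, so every ward contributes its own pre-intervention count.

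The Data analysis section describes the model for ward-level outcomes as "appropriate mixed models with a fixed effect for ward gender, and a random intercept for the ward". Ward gender is the only covariate named. The following paragraph turns to patient and staff outcomes. There, with VOICE as the one exception, it says that baseline values may be used as a covariate. A statistical analysis plan is to be agreed before allocation is revealed; it is not at hand.

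The Sample size section powers the incident outcome for 16 wards per arm, "assuming 5.22 mean number of events in the control arm" and 3.13 in the intervention arm (a 40% reduction), "assuming a poisson distribution for the outcome". It claims more than 80% power. It expects wards to average 24 beds, with a range of 18 to 30. Under Trial design, minimisation uses Trust and ward gender only.

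**The concern.** The section fixes a covariate list for a co-primary outcome, and the obvious prognostic variable is not on it. An analyst who follows the text literally would fit the incident model without the ward's own history.

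Three features make this matter:

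- There are only 34 units, and the design balances neither prior incident rate nor ward size. A chance difference in either adds to the error of the treatment estimate.
- The two co-primaries are treated differently. The WEMWBS calculation builds in a baseline–endpoint correlation of 0.3 and promises further covariate adjustment to protect 85% power. The incident outcome has the lower stated power and gets neither.
- The incident power figure assumes pure Poisson counts, so all wards in an arm share one rate. The planned random ward intercept allows for rates that differ between wards. If they do differ, the baseline count is the readiest way to recover some precision.

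**Working it through.** **Inputs.** From Sample size: means 5.22 and 3.13, 16 wards per arm, Poisson, beds 18–30 with mean 24. Assumed: two-sided 5% (the protocol states 5% only for WEMWBS); one count per ward; the same mean of 5.22 at baseline; and two quantities the protocol does not give. These are k, the squared between-ward CV of the incident rate, and ρ, the correlation of ward log-rates between baseline and follow-up.

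**1. The plan's own figure.**
- Difference scale: Φ(2.09/√((5.22 + 3.13)/16) − 1.96) = 82.5%.
- Log-rate scale: ln(3.13/5.22) = −0.511; variance (1/5.22 + 1/3.13)/16 = 0.0319; Φ(0.511/0.179 − 1.96) = 81.6%.
- Square-root scale: Φ(2(√5.22 − √3.13)/√(2/16) − 1.96) = 83.1%.

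The claim of more than 80% is confirmed, with about 2 to 3 points to spare. For comparison, WEMWBS with 9 per ward, ICC 0.05 and correlation 0.3 gives 85.2% at 16 wards per arm.

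**2. Between-ward variation and baseline adjustment.** On the log scale the variance without adjustment is (1/5.22 + k + 1/3.13 + k)/16. Adjusting for the baseline count replaces k by k(1 − ρ²·k/(k + 1/5.22)). The ratio k/(k + 1/5.22) allows for Poisson noise in the baseline count itself.

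Example, k = 0.2 and ρ = 0.7: the ratio is 0.2/0.392 = 0.511, so k becomes 0.2(1 − 0.49 × 0.511) = 0.150. The variance falls from 0.0569 to 0.0507 and power rises from 57.3% to 62.2%.

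| k | unadjusted | adjusted, ρ = 0.7 | adjusted, ρ = 1.0 | gain (points) |
|---|---|---|---|---|
| 0 | 81.6% | 81.6% | 81.6% | 0 |
| 0.1 | 67.9% | 70.0% | 72.3% | 2.1 to 4.4 |
| 0.2 | 57.3% | 62.2% | 68.2% | 4.9 to 10.9 |
| 0.5 | 38.4% | 47.7% | 63.5% | 9.3 to 25.1 |

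**3. Cross-check by simulation.** Quasi-Poisson GLM with t reference, 16 wards per arm, beds uniform on 18–30, 1,000 trials per setting, with log(baseline + 0.5) as covariate:
- k = 0: 74.8% without adjustment, 74.0% with it.
- k = 0.1: 62.2% to 62.7% (ρ = 0.7); 60.9% to 66.6% (ρ = 1).
- k = 0.2: 55.4% to 57.1%; 54.8% to 61.8%.
- k = 0.5: 36.8% to 47.3%; 37.5% to 58.0%.

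The pattern is the same, with somewhat smaller gains in most settings.

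**4. Ward size.** Beds uniform on 18–30 have SD 12/√12 = 3.46 and CV 3.46/24 = 0.144, so k = 0.021 if incidents are proportional to beds. Log-scale power is then 78.6%, and a perfect bed offset restores 81.6%, a gain of 3 points. In the simulation the offset alone gained about 1 to 3 points.

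**The case against.** The strongest reply is that this is detail for the statistical analysis plan. The protocol speaks only of suitable mixed models. Its list cannot be complete, because it does not name time, although follow-up counts come at three points, or Trust, although it is a minimisation factor. The baseline sentence exempts only VOICE and could be stretched to cover incidents. A random ward intercept for a ward-level count makes most sense with repeated counts, and baseline might be one of them. This much stands: a reader might infer that the plan rules baseline adjustment out, and the text does not support that. It supports only that the adjustment is not named for this outcome and is optional where it is named.

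The size of the gain is also fairly challenged. A reader might take it that a known amount of power is being given away. The documents give neither k nor ρ, and under the protocol's own Poisson assumption nothing is gained. The calculations use one count per ward and a simple count model, so they are not the power of the planned mixed model. Chance imbalance under randomisation is imprecision, not bias.

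Finally, a reader might want an exposure offset in occupied bed-days. The documents do not support that as the primary analysis. Bed-days in follow-up are measured after randomisation, and the Outcome measures section expects better patient outcomes to shorten admissions, so treatment could change the denominator. The offset would turn a total into a rate, and nothing shows that bed-days are part of the data request. The counting windows are already equal, and the 18–30 range is a survey estimate, not a description of the recruited wards.

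What remains is that a named model for a co-primary outcome leaves out a prognostic count that is already collected.

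**Conclusion.** The point holds as a recommended clarification, not as a flaw in validity. Ward gender is the only covariate named for the incident model, and the baseline count is available at no extra cost.

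The benefit is conditional: none if counts are pure Poisson, about 2 to 11 points of power at k = 0.1–0.2, and about 9 to 25 points at k = 0.5, for ρ between 0.7 and 1.0. Both k and ρ are assumptions.

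A reader might also infer that adjustment would rescue the sample size. It would not: at k = 0.2 adjusted power is 62–68%, still short of 80%. The absence of between-ward variation from the power calculation is a separate and larger matter. Ward size is secondary, worth about 1 to 3 points if beds are spread evenly over 18–30 and incidents scale with beds.

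**What to change.** State in the analysis plan, before allocation is revealed, that the ward-level count model includes the ward's baseline 3-month incident count as a covariate, for example log(count + 0.5), alongside treatment and ward gender. If baseline is instead to enter as one of the repeated counts, say so, and do not also use it as a covariate. Because the Recruitment section places baseline data collection after randomisation, define the baseline window as ending before the intervention starts.

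Optionally add log(staffed beds), fixed at baseline or preferably before randomisation, as a covariate or offset. Do not make occupied bed-days during follow-up the primary offset.

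The cost is a sentence of text and about one degree of freedom, or two if beds enter as a covariate. The baseline counts need no new data collection; the bed count is one extra figure per ward.

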## Methods

### Trial design

The study is a single blind, pragmatic, cluster randomised controlled trial. The TULIPS model will be delivered at the ward level (cluster) and compared to treatment as usual within a superiority framework, using a one-to-one allocation ratio, with minimisation based on Trust and ward gender (male/female/mixed). The trial will include a 9-month internal pilot which will have clearly defined stop/go criteria. The comparator was selected on the basis of pragmatics and difficulty in identifying a suitable control comparator.

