### Blinding and Randomisation

Once a site is recruited all eligible and consenting wards will be randomised. To maintain allocation concealment, the allocation will be conducted by an independent statistician at the King’s Clinical Trials Unit. Wards will be identified, and their Trust and ward gender (male/female/mixed gender) recorded. These will be entered into the minimisation program. If it does not make any difference to the balance on these variables which group is chosen, the ward will be allocated randomly. Otherwise, it will be allocated to the group which would make the two groups better balanced on these variables.

Members of the Trial Steering Committee (TSC), study statisticians, health economists and outcome assessors will be blinded to treatment allocation while the trial is ongoing. If the outcome assessors know (or suspect) they have been unblinded, this will be recorded on an unblinding form. For practical reasons linked to the setup and delivery of the intervention, some members of the research team and will not be blinded, including the Project Manager and Chief Investigator. Due to the nature of the intervention, participants and intervention delivers will not be blinded following the commencement of the intervention. Ward allocation will however, be concealed from potential participants until the completion of baseline measures to reduce the risk of selection bias.

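### Wards are minimised on Trust and ward gender, but the named models omit Trust throughout and omit both factors for WEMWBS, so the tests are conservative to the extent that these factors predict outcome

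*Protocol article*

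**What the plan says.** The Trial design section describes allocation "using a one-to-one allocation ratio, with minimisation based on Trust and ward gender (male/female/mixed" gender). Blinding and Randomisation makes the procedure deterministic except for ties: "If it does not make any difference to the balance on these variables which group is chosen, the ward will be allocated randomly". Otherwise the ward goes to whichever arm improves balance.

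The Data analysis section then names two families of model:

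- **Ward-level outcomes**, which include the serious-incidents co-primary: "Treatment effects for the cluster (ward) level outcomes will be estimated using appropriate mixed models with a fixed effect for ward gender", plus a random ward intercept. Trust is not named.
- **Individual-level outcomes**, which include the WEMWBS co-primary: these "will be analysed using an appropriate generalised linear mixed model with random intercepts for wards". Neither Trust nor ward gender is named. Except for VOICE, "the baseline values of the outcomes can be used as a covariate in the models".

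The only other statement on covariates is in Sample size: "Adjustments will be made for additional covariates in order to preserve 85% power against a larger observed ICC value", or against a weaker observed baseline-endpoint correlation. Those covariates are not named. A statistical analysis plan is to be agreed before allocation codes are revealed.

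**The concern.** Minimisation forces the arms to be alike on Trust and ward gender. If these factors affect outcome, the treatment difference varies less from one possible allocation to the next than it would under simple randomisation. A model without the factors does not know this. It leaves their variation in the between-ward variance and reports a standard error larger than the true one. Confidence intervals are then too wide, the type I error falls below 5%, and precision gained by the allocation is not used.

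The article is also uneven with itself. It carries one of the two factors into one family of models and neither into the other, and gives no reason. The Sample size sentence does not repair this, because it names no covariates and promises a power that unnamed covariates cannot guarantee.

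**Working it through.** **1. The plan's own figure (Sample size).** Inputs: effect 0.4 SD, ICC 0.05, baseline-endpoint correlation 0.3, 85% power, 5% significance (two-sided assumed), 34 wards, so k = 17 per arm.

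- Per arm before clustering: n = 2 × ((1.960 + 1.036)/0.4)² × (1 − 0.3²) = 102.1.
- Cluster size: m = n(1 − ICC)/(k − n × ICC) = 102.1 × 0.95/(17 − 5.11) = 8.16, rounded up to 9.
- Analysis set: 9 × 17 = 153 per arm and 306 in total. Dividing 306 by 0.80 gives 383. These agree with the article.
- SE at m = 9: √[(2/17) × 0.91 × (0.05 + 0.95/9)] = 0.129 SD. Power is 87.3% (normal) or 85.2% (t, 32 df).

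This calculation has no term for Trust or gender, so the planned 85% does not depend on adjusting for them.

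**2. WEMWBS with and without the minimisation factors.** Simulation of 34 wards minimised as described, 9 patients per ward, ICC 0.05, correlation 0.3, analysis of ward means, 1,500 trials per setting. Assumptions not in the article: 6 or 10 Trusts; a share f of between-ward variance due to the two factors, four fifths of it Trust. Adjustment is by fixed effects.

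| Trusts | f | Reported SE, unadjusted | True SE | Type I, unadjusted | Type I, adjusted | Power, unadjusted | Power, adjusted |
|---|---|---|---|---|---|---|---|
| 6 | 0 | 0.1288 | 0.1281 | 4.5% | 4.7% | 84.7% | 82.7% |
| 6 | 0.5 | 0.1281 | 0.1190 | 3.3% | 4.7% | 88.1% | 90.4% |
| 6 | 0.9 | 0.1269 | 0.1104 | 2.7% | 5.0% | 88.3% | 93.7% |
| 10 | 0 | 0.1294 | 0.1272 | 4.5% | 4.8% | 85.1% | 81.8% |
| 10 | 0.5 | 0.1280 | 0.1196 | 3.8% | 5.4% | 86.3% | 86.7% |
| 10 | 0.9 | 0.1282 | 0.1121 | 2.7% | 5.1% | 88.9% | 92.2% |

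Reported over true SE: 0.1281/0.1190 = 1.08 and 0.1280/0.1196 = 1.07 at f = 0.5; 0.1269/0.1104 = 1.15 and 0.1282/0.1121 = 1.14 at f = 0.9. With the article's SD of 8.7, the f = 0.5 case with 6 Trusts is 0.1281 × 8.7 = 1.11 points reported against 0.1190 × 8.7 = 1.04 true. Simulation error on power is about 1 point.

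**3. Serious incidents, illustration only.** Control mean 5.22 and a 40% reduction (Sample size); one count per ward; quasi-Poisson with gender, with and without fixed Trust terms; 1,000 trials per setting. Assumptions: 6 or 10 Trusts, log-scale ward variance 0.1.

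- Trust variance 0.1: power 57–58% without Trust, 64–65% with it.
- Trust variance 0.2: 48–50% without, 61–64% with.
- Trust variance 0: adjustment costs 2–5 points.
- Where Trust matters, type I error without Trust was 2.6–3.1%. With Trust it was 4.4–5.6% in five of the six settings and 7.5% in the other.

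A repeat with separate code gave the same pattern, with adjusted type I error of 5.5–7.0% where Trust mattered. Part of the apparent gain is therefore a slightly liberal test. The low absolute power comes from the assumed ward variance, not from omitting Trust.

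**4. The promise to preserve 85%.** At ICC 0.10: SE = √[(2/17) × 0.91 × (0.10 + 0.90/9)] = 0.146; 0.4/0.146 − 1.96 = 0.77; power 78%. To regain 85% with ward-level covariates, the between-ward term b must satisfy (2/17) × 0.91 × (b + 0.10) = (0.4/2.996)² = 0.0178. So b = 0.067, a cut of one third from 0.10, before any loss of degrees of freedom. Whether unnamed covariates reach that is unknown.

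**The case against.** The strongest reply is that this is a journal article, that both models are called appropriate, and that the full covariate list belongs to an analysis plan not shown here. That stands in part. The text does not exclude Trust or gender, and a reader who infers that they will be left out goes further than it allows. But the article does list adjustment terms, and the list does not match the allocation.

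A reader might also infer that power is lost outright, or that the trial falls short of 85%. The figures do not support this. Unadjusted power is 84.7 to 88.9% in every WEMWBS setting, so the plan is met within simulation error and only a possible gain is forgone. If the factors predict nothing there is no loss, and fixed Trust terms make matters worse. Larger losses for WEMWBS need an ICC well above the planned 0.05.

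For incidents, the article has reporting criteria reinforced in both arms and a 25% blinded check. Both may narrow differences between Trusts, so a larger loss there is possible but not shown.

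On the Sample size sentence, a reader might infer that outcome data will choose the model. It can equally describe planned adjustment as a hedge, with the analysis plan fixed before codes are revealed. A reader might also compute that regaining 85% at ICC 0.10 needs explained variance to rise from 9% to about 24%. That treats covariates as acting equally within and between wards; for ward-level covariates, one third of the between-ward variance suffices.

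**Conclusion.** The point holds in a conditional form. The named models do not carry both minimisation factors: ward gender is in the ward-level model only, and Trust is in none. Unless the analysis plan adds them, the WEMWBS test is conservative to the extent that Trust and gender predict outcome. At ICC 0.05, with 6 or 10 Trusts and 50 to 90% of between-ward variance explained (all three of these last figures assumed), the standard error is about 7 to 15% too large, type I error is about 2.7 to 3.8%, and 0 to 5 points of power are forgone, with 85% still met. There is no added false-positive risk from the omission. The effect on serious incidents may be larger, but its size rests on assumed variances. Separately, the 85% power is secured only under the assumed ICC and correlation, and the Sample size sentence promises more than that.

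**What to change.** - Include ward gender (fixed) and Trust in the models for primary and secondary outcomes. Fit Trust as random, or as fixed if there are few Trusts. For incident counts, check the type I error of the chosen form by simulation before it is fixed.
- State that the baseline value is a covariate wherever it was collected, as a rule and not an option. This cannot cover VOICE, or the patients newly recruited at 6 months, who complete WEMWBS without a baseline.
- In Sample size, replace the sentence on additional covariates with a statement that covariates are prespecified and that 85% power holds under ICC 0.05 and correlation 0.3, falling to about 78% at ICC 0.10.

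The cost is wording, since both variables are recorded at allocation. Statistically, fixed Trust terms use 5 to 9 ward-level degrees of freedom with 6 to 10 Trusts. If Trust and gender are unrelated to outcome, that costs about 2 to 4 points of power for WEMWBS. A random Trust effect uses fewer.

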## Objectives

The primary objectives are: i) to assess the effectiveness of a psychological service model designed specifically for acute mental health wards; and ii) determine whether it reduces the occurrence of ward-level serious incidents and improves patient wellbeing. Secondary objectives are to: assess whether the intervention improves patient and staff perceptions of ward atmosphere, staff burnout, patient mental health symptoms and functioning; and to explore patient resource use to assess the cost-effectiveness of the psychological service model.

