During the ward recruitment period, all staff on the ward and all patients on the ward meeting inclusion criteria will be approached about the study. Researchers will base themselves on the wards during the recruitment periods in order to promote the study and maximise opportunities for recruitment. Staff and patients will be provided with a written copy of the participant information sheet describing the details of the study. Where possible, potential participants will be given at least 24 hours to decide whether or not they would like to participate. However, if a participant wants to take part before this 24-hour window, we will give them the opportunity to do so. In all instances, participants will be provided with the opportunity to read the participant information sheet, be provided with the opportunity to ask questions about the research, and have their questions answered satisfactorily. They will be asked to consent to completing self-reported outcome measures and/or consent to take part in a qualitative interview. The information sheet and consent form will state that their participation is entirely voluntary and that they are free to withdraw from the study at any point. It is likely that most of the patients recruited at baseline will be discharged before the follow-up period. Therefore, follow-up measures will be completed in community settings. Researchers will take a proactive approach to follow-up assessment which will involve multiple attempts to contact people and being flexible with appointment times and locations, including the possibility of conducting follow-ups via email/ Microsoft Teams (staff) and/or phone (staff and patients).

Separate consent will be sought from patients on the ward at 6-month follow-up to complete the Views on Inpatient Care (VOICE; [20]). This is because it is likely different patients who will need to be recruited from baseline given the probability that the same patients will no longer be on the ward. Although participants will not be blind to the treatment condition of the ward, there will be a separate participant information sheet for the VOICE, which will not explicitly refer to the fact that the study is testing the effects of providing psychological therapies on inpatient wards. Potential participants will be informed that the study is assessing patient satisfaction with wards with different compositions of multidisciplinary team members**.**

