**Patient Measures**			
Informed consent	x	x (VOICE participants)	
Demographics	x	x (VOICE participants)	
Brief Symptom Inventory (BSI; Derogatis, 1993)	x	x	x
Personal and Social Performance Scale (PSP; Morosini et al, 2000)	x	x	x
Quality of Life (EQ-5D-5L)	x	x	x
Views on In-Patient Care (VOICE; Evans et al, 2012)		x (VOICE participants)	
Warwick-Edinburgh Mental Well-being Scale (WEMWBS; http://www2.warwick.ac.uk/ fac/med/research/platform/)	x	x (including VOICE participants)	x
Health Economic (HE) Measure	x	x	x

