**Staff Measures**			
Informed consent	x		
Maslach Burnout Inventory (MBI; Maslach & Jackson, 1981)	x	x	x
Views on Therapeutic Environments (VOTE; Laker et al, 2012)	x	x	x

All outcome assessors will receive training in the outcome measures from the project team and have access to supervision from a clinically qualified investigator during data collection periods. As detailed in the data management section below, all sites will also be subject to data monitoring which will include compliance with completion of outcome measures.

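### Patient-rated ward atmosphere (VOICE) has no baseline, which costs some precision and leaves its 9 patients per ward slightly short of the specified 85% power

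*Protocol article*

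**What the plan says.** The Objectives include a secondary aim to "assess whether the intervention improves patient and staff perceptions of ward atmosphere". In Table 1 the patient scale, VOICE, has a single entry, at 6 months, marked "x (VOICE participants)". Every other patient and staff outcome questionnaire in that table has a baseline entry: BSI, PSP, EQ-5D-5L, WEMWBS, the health economic measure, MBI, and VOTE, the staff counterpart of VOICE. The Data analysis section states the consequence: "With the exception of patient ward atmosphere (VOICE), the baseline values of the outcomes can be used as a covariate in the models".

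The Recruitment section gives the reason. "Separate consent will be sought from patients on the ward at 6-month follow-up to complete the Views on Inpatient Care", and then: "This is because it is likely different patients who will need to be recruited from baseline", since the earlier patients will probably have left the ward.

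The Sample size section derives 9 analysed patients per ward for WEMWBS and the other individual-level secondary outcomes, allowing for a baseline-endpoint correlation of 0.3. It then uses the same 9 per ward for the patients recruited at 6 months to complete VOICE.

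**The concern.** The stated reason rules out a baseline from the same individuals. It does not rule out a baseline for the ward. VOICE asks patients about the ward, so the ward's mean score before the intervention is a usable covariate whoever supplied it. About 11 patients per ward are recruited on the ward just before the intervention starts and already complete a battery of measures. The article does not say why VOICE is left out of that battery.

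Two things are at stake. First, with 17 wards per arm, minimised only on Trust and ward gender, arms that differ in atmosphere by chance at the outset cannot be adjusted on that measure. Second, the VOICE sample of 9 per ward relies on a variance reduction that an outcome without a baseline cannot have.

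**Working it through.** **Inputs from the Sample size and Trial design sections:** 34 wards allocated 1:1, so k = 17 per arm; effect d = 0.4 SD; ICC = 0.05; baseline-endpoint correlation r = 0.3; 85% power; 5% significance (two-sided assumed); 20% attrition; 11 patients per ward at baseline and 9 VOICE respondents per ward at 6 months.

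**Reproducing the plan's figure**
- Individually randomised: n = 2 × ((1.960 + 1.036)/0.4)² = 112.2 per arm.
- With r = 0.3: 112.2 × (1 − 0.09) = 102.1.
- With k fixed: m = n(1 − ICC)/(k − n × ICC) = 102.1 × 0.95/(17 − 5.11) = 8.16, rounded up to 9.
- 9 × 17 = 153 per arm, 306 in all; 306/0.8 = 383 at baseline.

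All four stated figures reproduce. Power at m = 9 is 87.3% (normal) or 85.2% (noncentral t, 32 df).

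**The same calculation for VOICE, r = 0**
- m = 112.2 × 0.95/(17 − 5.61) = 9.36, rounded up to 10.
- At m = 9: SE = √(2 × (1 + 8 × 0.05)/(17 × 9)) = 0.135, and 0.4/0.135 gives 84.1% power (normal) or 81.8% (t).
- At m = 10: 86.5% (normal) or 84.4% (t). So 10 meets the target by the normal formula and falls just short on the t reckoning.

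**Chance imbalance.** The SD of the between-arm difference in true ward means is √(2 × ICC/17). This is 0.077 SD at ICC 0.05, against a target of 0.4 SD.

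**Gain from a ward-mean baseline.** Let s be the correlation of true ward effects between baseline and 6 months; the article does not give it, so 0.5 to 1.0 is assumed. Different patients respond at the two times.
- Reliability of the ward mean: baseline 11 × ICC/(1 + 10 × ICC); follow-up 9 × ICC/(1 + 8 × ICC).
- Gross variance reduction r² = s² × the product of the two. At ICC 0.05 the product is 0.367 × 0.321 = 0.118.
- Approximate cost of one ward-level covariate with 34 wards: variance multiplied by 1 + 1/(34 − 4) = 1.033.
- Net reduction = 1 − (1 − r²) × 1.033.

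| s (ICC 0.05) | Gross | Net |
|---|---|---|
| 0.5 | 2.9% | about 0 |
| 0.7 | 5.8% | 2.7% |
| 1.0 | 11.8% | 8.9% |

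Higher ICCs are assumptions only. At 0.10 the gross reduction is 7 to 28% over the same range of s, or about 4 to 25% net. At 0.20 it is 13 to 51% gross, or about 10 to 49% net.

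**The case against.** A reader might infer that a 6-month difference in VOICE could not be told apart from wards that already differed, and so that the comparison is biased. The documents do not support that. Wards are randomised, with minimisation on Trust and ward gender, so earlier differences do not favour either arm in expectation. The random ward intercept carries the remaining ward variation into the standard error. Nor does the word improves in the objective call for a baseline: within a superiority comparison against treatment as usual, a post-intervention contrast answers it.

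The other side also has fair points on size and cost:
- At the only ICC in the article the gain is small. It disappears if ward atmosphere is only moderately stable over six months.
- The patients are acutely unwell and already complete several measures within a 45-minute limit. The length of VOICE is not stated.
- VOICE is deliberately given under its own information sheet, which does not mention the test of psychological therapies. A baseline VOICE in the main battery would come under the main sheet, which may weaken its correlation with the 6-month score.
- Baseline data are gathered after randomisation, with a selection risk that the Recruitment section admits. However, allocation is to be concealed from potential participants until baseline measures are complete.

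These points limit the benefit. They do not explain why no ward-level baseline is taken, and they leave untouched the use of r = 0.3 for an outcome with no baseline.

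**Conclusion.** The point holds as a minor one about efficiency. VOICE alone lacks a baseline, so existing ward differences in patient-rated atmosphere cannot be adjusted for directly; ward gender, Trust or baseline VOTE could act only as partial proxies. What is lost is precision and protection against chance imbalance.

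The firmest part uses only the protocol's inputs: without the 0.3 correlation, 9 per ward give about 82 to 84% power, not 85%. This is a small shortfall on a secondary outcome. The benefit of a ward-mean baseline depends on the assumed stability, and is about 0 to 9% of the variance at ICC 0.05. A larger benefit requires a higher VOICE ICC, for which the article offers no figure.

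**What to change.** Add VOICE to the baseline column of Table 1 for patients recruited on the ward, and use the ward's mean baseline VOICE as a ward-level covariate in the 6-month VOICE model. The Data analysis sentence that excepts VOICE would then read that adjustment is at ward level.

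If baseline VOICE is not feasible, state in the Sample size section that VOICE has no baseline and that 9 per ward give about 82 to 84% power, or recruit 10 per ward (86.5% normal, 84.4% t).

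The cost of the first option is one more form inside the 45-minute limit, and a baseline taken under a different information sheet from the follow-up. The second needs only a corrected statement or one more patient per ward. Ward-mean baseline VOTE, already collected, is an optional proxy covariate, but its correlation with VOICE is not documented and no gain should be assumed from it.
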